## Abstract

**Background:**

Existing primary care cognitive assessment tools are crude or time-consuming screening instruments which can only detect cognitive impairment when it is well established. Due to the COVID-19 pandemic, memory services have adapted to the new environment by moving to remote patient assessments to continue meeting service user demand. However, the remote use of cognitive assessments has been variable while there has been scant evaluation of the outcome of such a change in clinical practice. Emerging research in remote memory clinics has highlighted computerized cognitive tests, such as the Integrated Cognitive Assessment (ICA), as prominent candidates for adoption in clinical practice both during the pandemic and for post-COVID-19 implementation as part of health care innovation.

**Objective:**

The aim of the Accelerating Dementia Pathway Technologies (ADePT) study is to develop a real-world evidence basis to support the adoption of ICA as an inexpensive screening tool for the detection of cognitive impairment to improve the efficiency of the dementia care pathway.

**Methods:**

Patients who have been referred to a memory clinic by a general practitioner (GP) are recruited. Participants complete the ICA either at home or in the clinic along with medical history and usability questionnaires. The GP referral and ICA outcome are compared with the specialist diagnosis obtained at the memory clinic. The clinical outcomes as well as National Health Service reference costing data will be used to assess the potential health and economic benefits of the use of the ICA in the dementia diagnosis pathway.

**Results:**

The ADePT study was funded in January 2020 by Innovate UK (Project Number 105837). As of September 2021, 86 participants have been recruited in the study, with 23 participants also completing a retest visit. Initially, the study was designed for in-person visits at the memory clinic; however, in light of the COVID-19 pandemic, the study was amended to allow remote as well as face-to-face visits. The study was also expanded from a single site to 4 sites in the United Kingdom. We expect results to be published by the second quarter of 2022.

**Conclusions:**

The ADePT study aims to improve the efficiency of the dementia care pathway at its very beginning and supports systems integration at the intersection between primary and secondary care. The introduction of a standardized, self-administered, digital assessment tool for the timely detection of neurodegeneration as part of a decision support system that can signpost accordingly can reduce unnecessary referrals, service backlog, and assessment variability.

**Trial Registration:**

ISRCTN 16596456; https://www.isrctn.com/ISRCTN16596456

**International Registered Report Identifier (IRRID):**

DERR1-10.2196/34475

## Introduction

Worldwide, national dementia strategies emphasize the need for improving the diagnostic pathway at the point of primary care toward timely diagnosis. Currently, general practitioner (GP) clinical judgement of cognitive impairment is the basis of referral initiation to specialist services. Existing primary care cognitive assessment tools (eg, the General Practitioner Assessment of Cognition [GPCOG], the Mini-Cog, and the Six-Item Cognitive Impairment Test [6CIT]), are crude or time-consuming screening instruments which can only detect cognitive impairment when it is well established. Dementia is difficult to diagnose; in a study concerning false positive diagnoses, 60% of GPs misdiagnosed dementia [1]. More detailed tests deployed in secondary care are expensive and often physically and psychologically intrusive for the patient (eg, lumbar puncture). As a result, many false positives are identified in referred patients. A key limitation of existing screening tests is the lack of robust evidence to support them; few have been well validated in the populations for which they are intended.

Figure 1 demonstrates the dementia diagnostic pathway for patients. Patients who are referred by their GP are triaged. At the memory clinic, patients undergo 2 appointments; the first is typically conducted by a nurse and involves administration of a cognitive assessment. At the second appointment (the diagnostic clinic visit), conducted by a dementia medical specialist, the patient receives the outcome of the assessment (see “Outcomes” within Figure 1 for examples of typical outcomes).

**Figure 1 figure1:**
[figure not shown]
Dementia diagnostic pathway for patients.

The COVID-19 pandemic has effectively brought clinical practice in the memory services to a standstill. Nationally, memory services have adapted to the new environment by moving to remote patient assessments to continue meeting service user demand while reducing viral transmission [2]. However, the remote use of cognitive assessments has been variable, while there has been scant evaluation of the outcome of such a change in clinical practice [3]. Emerging research in remote memory clinics has highlighted computerized cognitive tests, such as the Integrated Cognitive Assessment (ICA), as prominent candidates for adoption in clinical practice both during the pandemic and for post-COVID-19 implementation as part of health care innovation [4].

The ICA is a 5-minute computerized cognitive test based on a rapid categorization task that employs an artificial intelligence model to improve its accuracy in detecting cognitive impairment [5]. The ICA is self-administered and independent of language [6,7]. The value proposition of the ICA is that an accurate and sensitive tool for diagnosis will streamline the diagnosis of dementia by reducing false positive results from GP referrals and, therefore, minimizing the need for further, expensive and time-consuming assessments.

In order to address this challenge, we initiated the Accelerating Dementia Pathway Technologies (ADePT) study. The intention of conducting this study is to develop a real-world evidence basis to support the adoption of ICA as an inexpensive screening tool for the detection of cognitive impairment to improve the efficiency of the dementia care pathway.

The ADePT study is an ongoing multicenter real-world evidence study. The objective of ADePT is to deliver real-world evidence on practices and the economic case for ICA adoption in memory clinics for the assessment of cognitive impairment associated with dementia, Alzheimer Disease (AD), mild cognitive impairment (MCI), and similar diseases, including the assessment of preferred business models by comparing the accuracy of GP referrals against the ICA.

## Methods

### Ethics Approval

Health Research Authority and Health and Care Research Wales approval for this study was obtained in February 2020. The study is registered in the ISRCTN Registry (ISRCTN16596456).

### Study Design

All participants are recruited among attendees at the National Health Service (NHS) memory services at the point of referral by their GP. The participants who do not have a formal diagnosis of a neurodegenerative disease are triaged as per usual clinical practice and are asked to complete the ICA in parallel with the diagnostic assessment. The aim of the clinical work package is to recruit 140 participants into the study.

The main study inclusion criterion is referral to the memory clinic by a GP. Patients recruited must be 55 to 90 years old. Potential participants must also be fully informed of and understand the objectives, procedures, and possible benefits and risks of the study and have the capacity to provide written consent.

Subjects that meet the following criteria will be excluded from the study cohort:

Lack of capacity to consent to participation in this studyUpper limb arthropathy or motor dysfunction that limits the use of a tablet computerVisual impairment severe enough to limit the use of a tablet computerKnown diagnosis of dementiaAlready receiving cholinesterase inhibitors and/or Memantine

### Study Procedures

Participants enrolled in the study will be required to attend 1 visit at a designated memory clinic or remotely at their home (Assessment Visit 1 [AV1]). Participants will be asked to complete the ICA. Prior to taking the ICA, participants will also be requested to view a short training video to assist them in completing the task successfully. After taking the ICA, patients will complete the following short questionnaires:

Inquiry on stimulants, fatigue, and sleep: A questionnaire that assesses the participant’s overall state. Questions revolve around recent intake of stimulants (eg, coffee or alcohol), sleep quality, energy levels, and mood. The questionnaire is used in conjunction with the ICA to determine whether any of these factors have had an impact on ICA performance.ICA Usability Questionnaire: A questionnaire that assesses the participant’s views on their experience with the test to receive acceptability and usability feedback for the ICA.Cognitive Health Questionnaire: A questionnaire that assesses the participant’s history of activities of daily living and physical and mental health comorbidities. The questions should ideally be answered by the informant (study partner) if available or by the participant if an informant is not present. The questionnaire is used in conjunction with the ICA to determine whether cognitive impairment detected by the ICA is due to MCI/dementia or other organic and/or treatable conditions.

Lastly, a brief medical history of the participants via electronic health care records will be obtained, mainly focusing on any cognitive tests that have been taken by the participants.

Participants will also be given the option to carry out a retest visit (Assessment Visit 2 [AV2]) whereby they are again given the chance to take the ICA test either remotely or face-to-face, complete a usability questionnaire, and respond to inquiries on stimulants, fatigue, and sleep. The overall study pathway for participants is detailed at a high level within Figure 2.

**Figure 2 figure2:**
[figure not shown]
Accelerating Dementia Pathway Technologies (ADePT) study participant pathway.

### Data Management

The primary data sources are the Castor electronic data capture (EDC) system and the ICA portal. Castor EDC will be used to report all protocol-required information for each participant in the form of an electronic case report form. The participants of the study are not identified by name or initials on the electronic case report form or any other study documents to be collected by Cognetivity Neurosciences Ltd, but will be identified by a participant ID number. Data entry is performed by the researchers in the investigator sites, while data source verification is performed by the sponsor’s clinical research associate.

The ICA portal is a secure portal where ICA results are uploaded. In addition, the participant’s ID number and demographic details are also uploaded to the ICA portal, which allows linking of the ICA data to the Castor EDC data. Data entered in the iPad (Apple Inc) do not undergo source data verification; however, the ID field and key fields which are common between the ICA and EDC undergo a data check by the data manager and queries are raised in case of discrepancy.

The secondary data source is source data, which includes any information in original records and certified copies of original records of participants, including medical history records as well as worksheets, which are usually used in order to record protocol-required information during the assessment of each participant (eg, usability questionnaires) prior to inputting such data into Castor EDC.

Data linkage and processing then takes place, from which metrics and data sets for analysis are generated. Such metrics include, but are not limited to, demographic breakdown (to track the distribution of age, years of education, and gender), a spreadsheet of key data fields used by the Medical Monitor to review data for a patient as well as site metrics on recruitment, queries and protocol deviations, lock and sign off, study exit, and adverse events. 

### Statistical Analysis

For the purposes of these analyses, patients referred to the memory clinic are divided into the following 3 groups, based on their memory clinic outcome: (A) those who receive a diagnosis of MCI or dementia, (B) those who are identified as healthy or receive a diagnosis of a brain or mental disorder other than MCI or dementia, and (C) those who receive an inconclusive diagnosis.

Participants with an inconclusive outcome after the memory clinic assessment are excluded from further analysis. 

Participants in group A are counted as correct GP referrals. Participants in group B are counted as unnecessary or incorrect referrals.

#### Comparison with Specialist Diagnosis of MCI/Dementia

The metrics for GP referrals that will be calculated are the following:

Total number of patients referred by GPs=A+B+CProportion of necessary GP referrals (excluding inconclusive)=A/(A+B)Proportion of unnecessary GP referrals (excluding inconclusive)=B/(A+B)

Likewise, the following complementary metrics for the ICA will be calculated:

Total number of patients the ICA would have referred Proportion of patients correctly referred by the ICA Proportion of patients incorrectly referred by the ICA Proportion of patients correctly not referred by the ICA Proportion of patients incorrectly not referred by the ICA 

In a secondary outcome analysis, we will compare with specialist diagnosis of all types of cognitive impairment (those due to MCI, dementia, or other neurological or mental disorders).

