## Discussion

In summary, the ADePT project aims to improve the efficiency of the dementia pathway at its very beginning and supports systems integration at the intersection between primary and secondary care. The introduction of a standardized, self-administered, digital assessment tool for the timely detection of neurodegeneration as part of a decision-support system that can signpost accordingly can reduce unnecessary referrals, service backlog, and assessment variability.

Remote assessments in the post-COVID-19 clinical environment are expected to form a core part of frontline service delivery as both services and their service user attitudes change while the use of smartphones and tablet computers is expanding in older adults [8]. Early identification is key as evidenced by the Prime Minister’s Challenge in 2020 [9] and is now corroborated by the advent of novel disease-modifying treatments [10].

We hypothesize that the health economic benefits for such a decision support tool will overshadow the relatively low price of such a proprietary technology compared to pen and paper conventional tests that demand time and expertise most primary care practitioners may not have, in combination with limitations in their validity in prodromal dementia and invariable cultural and interpretation bias.

The main strength of this study is that it accommodates face-to-face and remote assessments as part of day-to-day practice in a memory service setting with minimal disruption to the pathway, while obtaining real-world data on participant experience and the acceptability of such a tool in a rapidly changing technological environment.

In the ADePT study, we investigate GP referrals to memory clinics, where GP colleagues have already made the clinical decision to refer to specialists. As a result, these cases may only be assessed as true or false positives based on prospective diagnosis of neurodegeneration or not.A more complete picture of the quality of primary care cognitive assessment would also require the study of true and false negatives (ie, those patients who were not referred to memory clinics by their GPs). This is a limitation of the study, albeit an unavoidable one as the latter would require multisite recruitment from GP surgeries and prospective participant follow-up which would be impractical. However, we expect that the ADePT results can inform a future longitudinal study in primary care.

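### With every participant already referred by a GP, the GP-versus-ICA contrasts have a fixed sign on the natural denominator, and the accuracy objective cannot be met as worded

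*Protocol article*

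**What the plan says.** Under Study Design, the protocol article states: "The main study inclusion criterion is referral to the memory clinic by a GP". The recruitment target there is 140, with no derivation.

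The Introduction presents the benefit of the ICA as "reducing false positive results from GP referrals" and describes the study objective as including an assessment made "by comparing the accuracy of GP referrals against the ICA".

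Under Statistical Analysis, conclusive patients fall into group A (MCI or dementia, a correct referral) and group B (anything else, an unnecessary or incorrect referral). Inconclusive patients (C) are dropped. The subsection on comparison with specialist diagnosis gives the GP metrics as formulas, A/(A+B) and B/(A+B). It continues: "Likewise, the following complementary metrics for the ICA will be calculated". A total and four proportions follow, covering correct and incorrect referral and correct and incorrect non-referral. One of them is "Proportion of patients incorrectly referred by the ICA". None has a formula or a denominator, and no rule is given for setting them against the GP metrics.

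The Discussion concedes, of the GP referrals, that "these cases may only be assessed as true or false positives". The Health Economic Evaluation section takes the comparison of ICA referrals with the specialist diagnosis as an input to its cost and time comparison.

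**The concern.** Comparing the accuracy of two referral rules requires that each can be right and wrong in both directions. Here the GP rule is positive for everyone, so it has no negatives to assess. Any second test applied to the same patients can only remove referrals. It must match or reduce the unnecessary ones, and it must match or reduce the correct ones.

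A statement that the ICA produced fewer unnecessary referrals than GPs would therefore hold for any test that leaves out at least one group B patient, whether or not it carries diagnostic information. That statement is also the benefit the Introduction puts forward. If it is reported as a finding about accuracy, or carried into the cost case without the missed cases, readers will credit the ICA with something the design guarantees.

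**Working it through.** **Inputs.** From the article: all participants are GP-positive; the GP metrics are A/(A+B) and B/(A+B); the target is 140. The only planning figure is the 140. It has no stated basis to reproduce, and nothing below depends on it beyond illustration. Not given, so assumed: the case mix A/(A+B), taken from 0.3 to 0.8; the share inconclusive, 0 to 20%; and the ICA referral rate q, 0.3 to 1.0.

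**Notation.** Against the specialist diagnosis, the ICA gives TP and FN in group A (TP + FN = A) and FP and TN in group B (FP + TN = B).

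**Step 1: sign of the contrasts on the A+B denominator.** FP ≤ B, so FP/(A+B) ≤ B/(A+B), which can only favour the ICA. TP ≤ A, so TP/(A+B) ≤ A/(A+B), which can only go against it. Both hold for every data set.

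**Step 2: an uninformative test.** Let it refer a share q regardless of diagnosis. In expectation TP = qA, FP = qB, FN = (1−q)A and TN = (1−q)B. Incorrect referrals are qB/(A+B), a fall of 1−q from the GP figure: 70% at q = 0.3, 50% at 0.5, 30% at 0.7 and none at 1. At q = 0.5 the figure goes from 0.70 to 0.35, 0.50 to 0.25, 0.40 to 0.20 and 0.20 to 0.10 for case mixes of 0.3, 0.5, 0.6 and 0.8. The inconclusive share does not alter these ratios. With group B as denominator the effect is the same (GP 1.0, test q).

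**Step 3: the share-of-referrals scale.** Here the uninformative test gives FP/(TP+FP) = qB/(qA+qB) = B/(A+B). This equals the GP figure for every q and case mix, so the apparent gain vanishes.

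**Step 4: an informative test alongside.** Take A = 84, B = 56, with none inconclusive. Compare a test with assumed sensitivity and specificity of 0.8 with two uninformative tests. The cells for q = 0.2 are 0.2×0.4 = 8%, 0.2×0.6 = 12% and 0.8×0.6 = 48%.

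| | Incorrectly referred /(A+B) | Correctly referred /(A+B) | Missed /(A+B) | Missed FN/A | TP/(TP+FP) |
|---|---|---|---|---|---|
| GP | 40% | 60% | 0% | 0% | 60% |
| Uninformative, q = 0.5 | 20% | 30% | 30% | 50% | 60% |
| Uninformative, q = 0.2 | 8% | 12% | 48% | 80% | 60% |
| Sensitivity = specificity = 0.8 | 8% | 48% | 12% | 20% | 85.7% |

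The last two rows have the same incorrect-referral figure, an 80% fall from the GP value. Only the other columns tell them apart.

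**Step 5: a formal test would not help.** In 200,000 simulated studies of 140 conclusive patients per case mix, an exact McNemar test of false positives in group B favoured a coin flip over GPs in more than 99.9% of studies at every case mix from 0.3 to 0.8, because all discordant pairs run one way. The article does not plan this test; it only shows that significance on this contrast would mean nothing. The coin flip's share of wrong referrals among its own referrals fell below the GP figure in 47% to 49% of draws, as chance would give.

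**The case against.** The strongest reply is that the plan reports all four ICA cells, not only incorrect referrals. As shares of A+B, together with A/(A+B), they determine sensitivity, specificity and both predictive values. A coin flip would be exposed by its halved correct referrals and its missed cases. That stands. A reader might infer that the planned summary cannot tell a useful ICA from a useless one, and the article does not support this. A reader might also infer that the design settles the whole comparison in favour of the ICA. It does not, because the correct-referral and missed-case contrasts are constrained the other way.

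Second, the ICA denominators are not stated. A full protocol or SAP, not shown, may define them, and if the denominator were ICA referrals the artefact would be absent. So it cannot be asserted that the ICA figures are on a different scale from the GP figures; with A+B they share the GP denominator. The A+B reading is natural because the items are worded as proportions of patients and the four outcomes partition the conclusive sample, but it remains a reading.

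Third, the Discussion discloses that GP negatives are absent, and the economic section already considers triage at entry to the memory clinic, for which avoided referrals against missed cases is the right trade-off. Both are true. The disclosure, however, concerns how fully primary care assessment can be judged. It does not say that the GP-versus-ICA contrasts become one-sided, and the objective is left as it is. No definition of denominators can supply GP negatives. Nor does the economic section say that missed cases are left out, so that should not be assumed; it simply does not say that they are carried through.

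**Conclusion.** The point holds in a limited form. As worded, the objective of comparing GP and ICA accuracy cannot be met, because GP sensitivity and specificity are fixed at 100% and 0% by recruitment. This needs no assumption. On the A+B denominator the sign of each GP-versus-ICA contrast is known before data, in the ICA's favour for unnecessary referrals and against it for correct ones. This rests on the natural reading of proportions whose denominators are not given.

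The size of the artefact for an uninformative test is a reduction of 1−q in unnecessary referrals at any case mix. It is tempting to say that a random test always halves them, but that needs a 50% referral rate, and the article gives no ICA referral rate. The planned metrics contain what is needed to interpret the ICA properly. The fault lies in which contrast the objective and the parallel listing put forward, and it should be corrected before the data are analysed.

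**What to change.** In the subsection on comparison with specialist diagnosis, and in the objective:

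1. State the denominator of each ICA proportion. Make ICA sensitivity TP/A and specificity TN/B, each with a 95% CI, the main accuracy result.
2. Compare GP and ICA on the share-of-referrals scale, TP/(TP+FP) against A/(A+B), with a CI that respects the pairing (both come from the same patients). Read it together with sensitivity, since predictive value alone can be raised by referring very few patients; one referral that happens to be a true case scores 100%.
3. Always report avoided unnecessary referrals jointly with missed cases FN/A, and carry both into the cost and time comparison in the Health Economic Evaluation.
4. Reword the objective as the added triage value of the ICA among GP-referred patients, and state in the Discussion that the design fixes the direction of the simple contrasts.

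The cost is wording and a few lines of analysis code, with no new data. The downside for the sponsor is a less favourable headline reduction in unnecessary referrals.
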